#### Blinding

This will be a single-blind RCT. The outcome assessor will be blinded to the subject allocation. The outcome assessor, who is independent from group allocation, will be responsible for outcome measurement. However, it would be hard to blind the participants given the nature of the intervention. This single-blind design may potentially expose the study to risks of bias in terms of performance, attrition, and evaluation and so inflate the treatment effects if the participants know their group allocation. Although blinding the participants to intervention assignment will be inapplicable in this study, various strategies will be used to minimize these risks. To minimize bias stemming from expectation, study participants will be blinded to the study hypotheses and details of study manuals, the information provided in the Informed Consent Form will follow the principle of equipoise by declaring uncertainty about the superiority of treatment effect of both arms [38]. Similar expected outcomes, such as improving general wellbeing, will be stated in the Information Sheet for both experimental and control groups. All participants will receive the same number of sessions of intervention and assessment. The participants will be reminded not to disclose their group status to the study assessor at any time point. This method is widely used to mask the outcome assessor from treatment assignment as recommended by the Evidence-based Behavioral Medicine Committee [39].

#### Attrition and missing data

Regarding attrition and missing data, an attrition rate of 25% is considered in this trial, and we will monitor the progress of the trial with respect to this target. To reduce attrition and missing data, the importance of full and complete participation in the trial, regardless of the treatment assignment, will be conveyed to the study team members and participants. Follow-ups will be arranged at participants’ convenience to minimize the burden of data collection. Participants will be contacted on telephone for follow-up arrangement, and two follow-up reminders will be delivered to participants, via telephone call or WhatsApp message at 2 weeks, and 1 day before follow-up. In order to facilitate a positive study experience among participants, all participants will be attentively followed up. All study procedures will be described clearly to the participants, and their performance assessment and its corresponding health implications will be explained individually at the end of each follow-up by the assessor. Contact information of participants will be kept up to date and reasons of dropout will be documented [40].

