#### Secondary outcomes

Secondary outcome measures will include the following: (1) motor symptoms, (2) mobility, balance, and fall risk, (3) spiritual wellbeing, and (4) HRQoL. Details of each outcome and instrument are as follows:
*Motor symptoms*
Movement Disorders Society – Unified Parkinson’s Disease Rating Scale – Part III Motor Examination (MDS-UPDRS-III) is an 18-item, assessor-rated instrument assessing severity of PD motor symptoms. Each item is scored “0” to “4” on a categorical scale, in which “0” indicates no impairment and “4” represents severe impairment. The total score is 132. Higher scores indicate more motor disabilities. This scale has demonstrated excellent internal consistency with a Cronbach’s alpha of 0.93. Excellent concurrent validity has been demonstrated by the good correlation with the original UPDRS (*r* = 0.96, *p* < 0.001) [45]
*Mobility, balance, and fall risk*
The Timed Up and Go test (TUG) is a simple test used to assess mobility, balance, and fall risk in older adults. It is used to count the time required for a participant to rise from a chair, walk for 3 m, turn around, walk back to the chair and sit down. Satisfactory test-retest reliability has been demonstrated in the PD population with intracluster correlation coefficient (ICC) ranging from 0.80 to 0.85 [46, 47]. Excellent concurrent validity has been demonstrated by good correlation with the Berg Balance Scale (– *r* = 0.78, *p* < 0.001) [48]. The minimal detectable change for the Chinese population with PD was 3.5 s [46]. The cutoff score for fall prediction among PD is 11.5 s with a sensitivity of 0.66 and specificity of 0.62 [35]
*Spiritual wellbeing*
The Holistic Well-being Scale (HWS) is a 30-item questionnaire that evaluate the two domains of holistic wellbeing, as follows: (1) the absence of affliction characterized by bodily irritability, emotional vulnerability, and spiritual disorientation and (2) the presence of equanimity in terms of general vitality, mindful awareness, nonattachment, and spiritual self-care. Each item is rated using a “0–10” scale, where “0” represents totally disagree, whereas “10” indicates totally agree. Higher scores indicate a worse state of holistic wellbeing. Satisfactory psychometric properties has been demonstrated in the Chinese version [49]
*HRQoL*

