### Data collection

The principal investigator will screen the eligibility of potential participants. For these eligible individuals, an Information Sheet of the study will be provided, and written informed consent will be sought. Information related to demographics and health background will then be collected (Appendix 3). All primary and secondary outcomes will be measured at baseline (T0), 2 months (T1; completion of intervention), and 3 months following the completion of the intervention (T2). All assessment will be conducted during the “on” state of medications to minimize motor fluctuations among participants. Participants will be instructed to follow their normal medication schedule and physical activity and not to start any new, instructor-led exercise program throughout the study period.

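### Having the blinded assessor give individual results feedback at T1 creates an avoidable risk of unblinding before the T2 motor ratings

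*Protocol article*

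**What the plan says.** The Blinding section makes the outcome assessor the only blinded party: "The outcome assessor will be blinded to the subject allocation". The same section gives that person the measurement task: "The outcome assessor, who is independent from group allocation, will be responsible for outcome measurement". Participants are not blinded, because "it would be hard to blind the participants given the nature of the intervention". The protection named for the visit itself is that "The participants will be reminded not to disclose their group status to the study assessor at any time point".

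The section on attrition and missing data then adds a retention measure. It opens with "In order to facilitate a positive study experience among participants, all participants will be attentively followed up" and goes on to say that "their performance assessment and its corresponding health implications will be explained individually at the end of each follow-up by the assessor".

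The Data collection section has every outcome assessed at three visits: T0 before the programme, T1 when it ends at two months, and T2 three months after that. Under Secondary outcomes, the MDS-UPDRS-III is described as an "18-item, assessor-rated instrument assessing severity of PD motor symptoms", and the TUG is a timed walking test. The Data analysis section compares the arms across all three time points by GEE.

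**The concern.** Two procedures in the article pull against each other. One asks participants to keep their allocation from the assessor. The other schedules a private talk between the same two people about how the participant performed and what that means for health. At T1 this talk comes just after eight weeks of yoga or exercise classes, when a remark about the class would be natural.

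If the assessor learns the allocation at T1, the T2 motor examination and the timed test may be done by someone who knows the arm. Blinding matters most for outcomes of this kind. The article itself, under Blinding and again under Limitations, lists evaluation among the sources of bias that could inflate the treatment effect, and it relies on its blinding strategies to contain that risk.

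A second, weaker route is that feedback at T1 could itself change what participants do or report before T2.

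**Working it through.** The article gives no figure for this point, so the check is mainly a reading of its sections against each other.

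1. **Who gives the feedback.** The attrition section says the assessor. The Blinding section speaks of the outcome assessor and the study assessor. No other assessor is named, so I take these to be one role.
2. **When.** Feedback is given at the end of every follow-up. The follow-ups are T1 (end of intervention) and T2 (three months later). Feedback at T1 comes after the T1 measurements and before those at T2. Feedback at T2 comes after the last measurement.
3. **Which ratings are exposed.** T1 ratings are complete before the T1 talk, and nothing is measured after the T2 talk. Only T2 ratings are exposed.
4. **Which outcomes.** Rater unblinding acts mainly on the MDS-UPDRS-III, a judgement-based rating, and on the TUG, which the assessor measures. The HADS, HWS and PDQ-8 are questionnaires. For them the relevant route is the content of the feedback.
5. **What removes the overlap.** The article does not give the feedback to another person, delay it until after T2, or provide for recording any unblinding.

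**Number exposed.** All participants who attend T1 are exposed. With 126 randomised, that is between 94 (2 × 47, if all the planned 25% attrition occurs before T1) and 126 (if none does). This counts people exposed to the talk; it does not measure bias.

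**Illustration under an assumed bias.** The sample size reproduces. A two-sample t-test with effect size 0.59, two-sided 5% and 80% power needs 46.08, so 47 per arm (power 0.808); 47 / 0.75 = 62.7, so 63 per arm and 126 in total. Nothing in this point changes those figures.

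The document gives no value for a rating bias, so I assume a between-arm bias b, in SD units, on one T2 outcome, with no true effect and 47 per arm. Then SE = √(2/47) = 0.206, and the two-sided error rate is 1 − Φ(1.96 − b/SE) + Φ(−1.96 − b/SE).

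| Assumed b (SD) | b/SE | Error rate (nominal 5%) |
|---|---|---|
| 0.1 | 0.48 | 7.7% |
| 0.2 | 0.97 | 16.3% |
| 0.3 | 1.45 | 30.7% |

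The table shows how sensitive the T2 test would be if such a bias arose. It is no evidence that one will.

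**The case against.** The strongest reply is that no loss of blinding has been shown. The article has the assessor explain results; it does not ask participants to describe their classes. The non-disclosure reminder applies at every time point and so covers this talk. Any visit that includes an 18-item motor examination already puts the assessor alone with an unblinded participant. There are also structural protections: the assessor is independent of allocation, the research coordinator handles the envelopes, and attendance is checked by the instructor and absences by the coordinator.

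Most of this stands. It makes unblinding a risk and not a certainty, and it means the reminder is the only safeguard at the visit but not the only one in the trial. It does not remove the overlap. The talk adds contact on the topic most likely to prompt a mention of the class, and measuring the outcomes does not require it.

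A reader might also infer that the primary outcome at T2, or every T2 contrast, is biased because participants are told their results. The document does not support that. Both arms receive feedback at the same visits, so a common effect cancels in the group comparison. Bias needs an effect that differs by arm, for example because T1 results differ or because an unblinded assessor gives different feedback. Nor does the article say that HADS scores are fed back: performance assessment may mean only the motor examination and the TUG. The main blinding weakness of the HADS is that participants know their arm, which the article openly acknowledges.

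Finally, the feedback has a purpose. With 25% attrition planned, postponing it gives up a retention incentive before the visit it is meant to protect.

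**Conclusion.** The point holds as a design weakness of limited reach. The article states a procedure that works against its own blinding: the one blinded party is assigned a one-to-one results talk with unblinded participants before the final ratings. What follows is an avoidable risk of assessor unblinding, bearing on two secondary outcomes (MDS-UPDRS-III and TUG) at one time point (T2). The T1 comparison is untouched. The T2 questionnaire contrasts, including the HADS, are affected only if the effect of feedback differs by arm.

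This rests on two assumptions: that the assessor in the attrition section is the blinded outcome assessor, and that the person who holds the T1 talk also rates the same participant at T2. The article suggests both by naming a single assessor role, but it does not state the second. The size of any bias cannot be derived from the document.

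**What to change.** Separate the feedback task from the blinded assessor, in one of two ways:

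- Have someone already on the team who does not assess outcomes, such as the research coordinator who carries out the allocation, give the feedback. This keeps its timing, but leaves in place any effect of the feedback itself on T2 scores.
- Defer individual feedback until after the participant's T2 measurements. This also removes the second route, but the retention incentive then comes later.

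In either case, have the assessor record any unblinding, or a guess of the allocation, at T1 and T2, so that the final report can say how well blinding held.

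The cost is a sentence or two in the procedures. The downside is that feedback comes from another person or later. If the coordinator takes it on, the sponsor should confirm that this role can explain the results, since the article does not say so. How safety-relevant results are handled is for the sponsor to decide and lies outside this point. Sample size, outcomes and the analysis model do not change.

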#### Adherence

All participants will be instructed to follow their normal medication schedule and physical activity and not to start any new instructor-led exercise program throughout the study period. All classes will be held at local community facilities. Picture-based education booklets with enlarged picture guides will be provided to participants to facilitate home-based practice (see Additional file 2: Yoga Educational Booklet). All participants will also be instructed to perform a 20-min, home-based practice twice a week. A self-reported activity log will be provided to monitor participants’ adherence to home-based practice. Class attendance will be checked by the instructor. Reasons for absenteeism will be also documented and verified by the research coordinator.

### Outcomes

#### Primary outcome

Psychological wellbeing in terms of anxiety and depression will be measured by the Hospital Anxiety and Depression Scale (HADS) [41, 42]. This scale has been suggested for use in the PD population as somatic symptoms that may potentially overlap parkinsonian manifestations are not assessed in this scale [43, 44]. The HADS consists of two subscales, namely, anxiety and depressive symptoms. Each subscale consists of seven items, and each item is rated by a four-point scale (range: 0–3). Levels of symptoms of anxiety and depression are considered clinically relevant at a cutoff value of ≥ 8 on each subscale and ≥ 15 for the full scale. The Chinese version of the HADS has demonstrated satisfactory validity and reliability with a Cronbach’s alpha of 0.86 for the overall scale, 0.82 for the depression subscale and 0.77 for the anxiety subscale [41, 42].

#### Secondary outcomes

Secondary outcome measures will include the following: (1) motor symptoms, (2) mobility, balance, and fall risk, (3) spiritual wellbeing, and (4) HRQoL. Details of each outcome and instrument are as follows:
*Motor symptoms*
Movement Disorders Society – Unified Parkinson’s Disease Rating Scale – Part III Motor Examination (MDS-UPDRS-III) is an 18-item, assessor-rated instrument assessing severity of PD motor symptoms. Each item is scored “0” to “4” on a categorical scale, in which “0” indicates no impairment and “4” represents severe impairment. The total score is 132. Higher scores indicate more motor disabilities. This scale has demonstrated excellent internal consistency with a Cronbach’s alpha of 0.93. Excellent concurrent validity has been demonstrated by the good correlation with the original UPDRS (*r* = 0.96, *p* < 0.001) [45]
*Mobility, balance, and fall risk*
The Timed Up and Go test (TUG) is a simple test used to assess mobility, balance, and fall risk in older adults. It is used to count the time required for a participant to rise from a chair, walk for 3 m, turn around, walk back to the chair and sit down. Satisfactory test-retest reliability has been demonstrated in the PD population with intracluster correlation coefficient (ICC) ranging from 0.80 to 0.85 [46, 47]. Excellent concurrent validity has been demonstrated by good correlation with the Berg Balance Scale (– *r* = 0.78, *p* < 0.001) [48]. The minimal detectable change for the Chinese population with PD was 3.5 s [46]. The cutoff score for fall prediction among PD is 11.5 s with a sensitivity of 0.66 and specificity of 0.62 [35]
*Spiritual wellbeing*
The Holistic Well-being Scale (HWS) is a 30-item questionnaire that evaluate the two domains of holistic wellbeing, as follows: (1) the absence of affliction characterized by bodily irritability, emotional vulnerability, and spiritual disorientation and (2) the presence of equanimity in terms of general vitality, mindful awareness, nonattachment, and spiritual self-care. Each item is rated using a “0–10” scale, where “0” represents totally disagree, whereas “10” indicates totally agree. Higher scores indicate a worse state of holistic wellbeing. Satisfactory psychometric properties has been demonstrated in the Chinese version [49]
*HRQoL*
The Parkinson’s Disease Questionnaire-8 (PDQ-8) is a short-form, 8-item questionnaire used to quantify the impact of PD on the HRQoL of patients [50]. This questionnaire assesses eight domains, as follows: mobility, activities of daily living, emotional wellbeing, stigmatization, social support, cognitions, communication, and bodily discomfort. A PDQ-8 summary index is generated. Higher scores indicate worse HRQoL. The internal consistency of the Chinese version of PDQ-8 has been validated with a Cronbach’s alpha of 0.87, and construct validity has been demonstrated against the Hoehn and Yahr scale and UPDRS motor scores [51]

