### Hypotheses

We hypothesize that (1) the structured mindfulness yoga program will be effective in improving psychological wellbeing, physiological wellbeing, spiritual wellbeing, and HRQoL in individuals with mild-to-moderate PD and (2) the structured mindfulness yoga program will be superior compared to stretching and resistance training exercise in improving psychological wellbeing, physiological wellbeing, spiritual wellbeing, and HRQoL in individuals with mild-to-moderate PD.

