### Sample size

According to a meta-analysis of the effects of yoga on depression compared with aerobic exercise, a moderate effect size of 0.59 was reported for individuals with elevated levels of depression.

In addition, a moderate-to-large effect size of 0.79 on anxiety was found when comparing yoga with relaxation [26]. To anticipate the effect size of at least 0.59 for our primary outcomes (depression and anxiety) and using the power analysis software Gpower 3.1, 47 subjects per arm give a two-arm RCT 80% power to detect an effect size of at least 0.59 at 5% level of significance. Considering previous RCTs of mind-body interventions among people with PD [20], an attrition rate of 25% is taken into consideration. Therefore, 126 subjects with 63 per arm will be recruited.

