### Data analysis

Descriptive statistics will be used to summarize the demographic, health conditions and clinical outcomes of the participants at three different time points. Normality of the variables will be assessed using the skewness statistic and normal probability plot. The two treatment groups will be examined, at baseline (T0), after the completion of intervention (T1), and 3 months after the completion of intervention (T2), for the changes in psychological distress, motor symptoms, mobility and balance, spiritual wellbeing, and HRQoL among participants. The intention-to-treat principle will be applied in all analyses. The intervention arm will be compared against the control for all primary analysis. Generalized estimating equation (GEE) models, specific with first-order, auto-regressive structure, will be used to assess the differential change of each primary outcome variable (HADS) and secondary outcome variable (MDS-UPDRS-III, TUG, HWS, and PDQ-8), across different time points between the two groups. Completers and noncompleters will be compared to examine any difference in demographic characteristics and health conditions. Prespecified subgroup analyses by gender, level of education, disease staging, and the presence of psychological distress will be conducted. IBM SPSS 22.0 software will be used for statistical analysis. All statistical tests will be two-tailed and statistical significance will be set at 0.05. The final report will follow the CONSORT 2010 guidelines as well as its extension to nonpharmacological interventions.

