### Pilot study

A pilot study of the yoga intervention was conducted from September to November 2016 [52]. Ten people with mild-to-moderate idiopathic PD were recruited with the same inclusion and exclusion criteria. Assessments were done before and after completion of this 8-weekly, 60-min yoga program to evaluate the feasibility of the yoga program. The enrollment rate was 58.8% and class adherence rate was 97.5%. There were no adverse events. Results of process evaluation are summarized in Table 3. All participants were satisfied with this program. Perceived benefits included improving flexibility, gait and balance, and reducing constipation, lessening back and shoulder pain, relaxing body and mind, increased ease of falling asleep, less anxiety, increased calmness, and better mood. From the preliminary data analysis, significant improvements were found for (1) psychological distress in terms of the HADS *(paired t test (T*
_*1*_
*–T*
_*0*_
*): mean = – 4.7 ± 4.16, p = 0.006)* and (2) holistic wellbeing in terms of affliction *(paired t test (T*
_*1*_
*–T*
_*0*_
*): mean = – 0.87 ± 0.80, p = 0.007)*. These findings support the hypothesis that yoga intervention can help PD individuals to improve their psychological wellbeing and change their perception of affliction.

**Table 3 Tab3:** Summary of process evaluation of pilot study (*n* = 10)

%	Strongly agree	Agree	No comment	Disagree	Strongly disagree
1. The content of exercise program is appropriate	60	30	10		
2. The total number of classes and duration of each class was appropriate − too short for each class (*n* = 1)	30	60		10	
3. The venue was appropriate	30	70			
4. I think that the difficulty level of exercise being taught in classes is appropriate for me	40	50	10		
5. I think that the breathing exercises are useful for me	40	60			
6. I think that the mindfulness meditation is useful for me	30	60	10		
7. I think that the yoga poses are useful for me	50	50			
8. The information being provided related to this exercise program is appropriate	40	50	10		
9. I am satisfied with the teaching methods delivered by the instructor	80	20			
10. I can remember the exercises learned from class	30	50	10	10	
11. In daily living, I have time to practice the exercises learned from class	30	60	10		
12. After the completion of exercise program, I am confident that I could continue the exercise practice in daily living	30	40	20	10	
13. Speaking overall, I am satisfied with this exercise program	50	50			

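### The Holistic Well-being Scale is given one scoring direction (higher is worse), but its equanimity domain, as the article describes it, is favourable when high

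*Protocol article*

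**What the plan says.** The Secondary outcomes section of the protocol article describes the HWS as a 30-item questionnaire with two domains. The first is "the absence of affliction characterized by bodily irritability, emotional vulnerability, and spiritual disorientation". The second is "the presence of equanimity in terms of general vitality, mindful awareness, nonattachment, and spiritual self-care". Every item uses one response scale, "where “0” represents totally disagree, whereas “10” indicates totally agree". The next sentence gives a single direction for the instrument: "Higher scores indicate a worse state of holistic wellbeing". The section mentions no reversed items, no direction by domain and no rule for a total.

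The Data analysis section names the HWS once, by abbreviation, in its list of each "secondary outcome variable (MDS-UPDRS-III, TUG, HWS, and PDQ-8". The Hypotheses section expects yoga to be "superior compared to stretching and resistance training exercise in improving psychological wellbeing, physiological wellbeing, spiritual wellbeing, and HRQoL". The Pilot study section reports one HWS result, "holistic wellbeing in terms of affliction", as a significant improvement: mean change -0.87 ± 0.80, p = 0.007, in ten participants. It gives no equanimity result.

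**The concern.** One direction cannot serve two domains that run in opposite directions on the same agreement scale. Agreeing with items on irritability, vulnerability or disorientation is bad. Agreeing with items on vitality, mindful awareness, nonattachment or spiritual self-care is good. The stated rule fits the first group and contradicts the second.

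The HWS is the trial's only measure of spiritual wellbeing, which is one of four objectives and part of the superiority hypothesis. Mindful awareness is an equanimity facet and also a main target of the yoga programme. The domain with the wrong label is therefore one in which the programme would be expected to show an effect. An analyst or reader who applied the sentence as written would report a higher equanimity score as deterioration.

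**Working it through.** **1. Direction, domain by domain.** The inputs are the domain descriptions, the response scale and the direction sentence in Secondary outcomes, plus the pilot result.

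| Domain | Meaning of agreement | Favourable direction | Stated rule |
|---|---|---|---|
| Affliction (3 facets) | more affliction | lower | correct |
| Equanimity (4 facets) | more equanimity | higher | wrong unless reversed |

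The item wording is not shown, so the second column is inferred from the facet names. For affliction, the pilot supports the inference, because a negative change is reported as an improvement. For equanimity, the article gives no result to check against, only the statement that its presence is part of wellbeing.

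**2. The article's one HWS figure.** For the paired t test, t = mean / (SD / √n) = -0.87 / (0.80 / √10) = -0.87 / 0.253 = -3.44 on 9 degrees of freedom. The two-sided p is 0.0074, which agrees with the stated 0.007. The affliction result is sound and is read in the right direction.

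**3. Domains scored separately.** Any equanimity change of +x is an improvement by the domain's definition and a worsening by the stated rule. The estimate and the two-sided p-value do not change. Only the interpretation is inverted.

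**4. Unreversed total (conditional illustration).** The article does not say that such a total is used. Assume that:
- *a* of the 30 items measure affliction, with *a* from 10 to 20 (the split is not given);
- affliction changes by -0.87 per item (the pilot value, taken as a per-item mean);
- equanimity changes by +x per item (no figure is given; two values are tried).

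Change in the unreversed item mean = [a × (-0.87) + (30 - a) × x] / 30. With equanimity reversed, the second term becomes -(30 - a) × x.

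| a | x = 0.50, unreversed | x = 0.50, reversed | x = 0.87, unreversed | x = 0.87, reversed |
|---|---|---|---|---|
| 10 | +0.04 | -0.62 | +0.29 | -0.87 |
| 15 | -0.19 | -0.69 | 0.00 | -0.87 |
| 20 | -0.41 | -0.75 | -0.29 | -0.87 |

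For example, with a = 10 and x = 0.87: (-8.7 + 17.4) / 30 = +0.29. Both domains improve in every row. The unreversed score nevertheless shows anything from a reduced benefit to a small net worsening, depending on inputs that the article does not supply.

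**The case against.** The strongest reply is that the harmful scenario is assumed. No section says that a 30-item total is computed or that equanimity items are left unreversed. With those items reversed, the direction sentence would be correct for a total. Item-level scoring may also sit in the full protocol or in the cited validation source, and an article may reasonably leave it there. This stands as far as offsetting is concerned.

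A reader might infer from the Data analysis section that a single collapsed HWS variable enters the model. The text does not support that. The list names instruments by abbreviation and treats the HADS in the same way, although the HADS has two subscales and the Sample size section calls depression and anxiety the primary outcomes. The pilot's separate affliction score suggests, if anything, that the team scores by domain.

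A reader might also count facets, three affliction against four equanimity, and conclude that equal improvement must register as net deterioration. That needs equal facet weights, equal effects and an unreversed sum. None of these is stated, and the table above shows that the sign changes with the assumed split.

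Finally, the description of equanimity itself tells a careful reader which way that domain runs, and the tests are two-tailed, so no p-value depends on the label. This is fair and limits the damage. It does not rescue the sentence, which states a direction for the whole scale and is wrong for one of its two described domains. That is an incorrect statement in the article, not detail left to another document.

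**Conclusion.** The direction sentence contradicts the article's own description of the equanimity domain. That finding rests on the outcomes text alone, with the modest assumption that agreement with equanimity items means more equanimity. Taken literally, the sentence turns an equanimity gain into a worsening. Because the pilot points to domain scoring, this misreading is the likelier risk.

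Offsetting in an unreversed total is possible but not established. Its size cannot be fixed from the article: under the assumptions shown, it runs from a partial loss of the benefit to full cancellation or a small change of sign. The documents do not support a claim that the planned analysis will cancel or reverse the spiritual-wellbeing effect.

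The point concerns the interpretation of one secondary outcome. The primary HADS analysis is unaffected, and so is the sample size, which rests on a standardised effect of 0.59 for depression and anxiety. Severity is moderate to minor.

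**What to change.** Replace the direction sentence in Secondary outcomes with: *Affliction: higher is worse; equanimity: higher is better.* Analyse the two domain scores as separate secondary outcomes, as the pilot did for affliction. If a single total is preferred, say so and reverse-score the equanimity items first; higher-is-worse then holds for that total. Either choice resolves the contradiction. It should be made before outcomes are compared by arm, and every HWS result in the report should carry its favourable direction.

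The cost is one sentence and, with separate domains, two outcome variables where the list now shows one abbreviation. No new data, visits or participants are needed.
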